### Sample Size

A meta-analysis of RCTs examining the effects of CBT in comparison to wait-list on depression in university students showed an effect size of 1.13 [34]. However, the effect sizes were smaller (0.56 [35] and 0.64 [36]) for studies in adults compared to those of internet-based and other computerized psychological treatments with wait lists. A meta-analysis of RCTs to examine the effectiveness of game-based digital interventions showed an overall effect size of 0.66 (against a wait-list control condition), 0.47 (with a target population of adolescent users), and 0.41 (type of game: psychoeducation and training, including the SPARX study) [22]. Additionally, a meta-analysis of RCTs to examine the effectiveness of technology-delivered interventions for depression and anxiety in children and adolescents showed an effect size of 0.45 compared to the wait-list group [37]. Considering these findings, we assumed a similar effect size (0.60) to that of internet-based and other computerized psychological treatments or game-based digital interventions against wait-list [22,35,36] for the reduction of primary outcomes assessed using Patient Health Questionnaire-9 (PHQ-9).

A power analysis showed that a target sample size of 90 was needed to detect an effect size of 0.60 with alpha=.05 and a power of 0.80 for a two-tailed test. Considering an anticipated 10% dropout [38], we will aim to recruit at least 100 (50 per group) participants to test the primary hypothesis of this study.

### Intervention

The treatment condition in this study consists of a game-based computerized CBT program called SPARX. It takes the form of an interactive fantasy game designed to take the user through seven modules that teach key CBT strategies. When the user begins SPARX, they meet the character of the Guide who introduces them to the “game world” and the challenges ahead, after which the user selects their avatar and begins the quest. Each module finishes with the avatar returning to the Guide who then explains how the “game skills” can be used in “real life”. The first module includes brief psychoeducation related to depression, with a brief introduction of relaxation (slow and controlled breathing) and hope. The remaining modules cover the following: activity scheduling/behavioral activation, interpersonal skills (communication, assertiveness, and negotiation), problem solving, cognitive restructuring (identifying common cognitive distortions and challenging negative thoughts), mindfulness, and relapse prevention (Textbox 1). Each module is designed to take about 20-30 min and the user is encouraged to practice the skills in the interim (the equivalent of homework).

Outline of content and core skills covered in each level of Smart, Positive, Active, Realistic, X-factor thoughts (SPARX).Level 1 (finding hope): psychoeducation about depression, introduction to the cognitive behavioral therapy model, introducing gloomy negative automatic thoughts and “hope” (people recover from depression), relaxation (controlled breathing)Level 2 (being active): activity scheduling, behavioral activation, relaxation (progressive muscle relaxation), basic communication, and interpersonal skillsLevel 3 (dealing with emotions): dealing with anger and hurt feelings, interpersonal skills (assertiveness, listening, and negotiation)Level 4 (overcoming problems): problem solving, cognitive restructuring (identifying smart, positive, active, realistic, X-factor thoughts)Level 5 (recognizing unhelpful thoughts): cognitive restructuring (recognizing different types of gloomy negative automatic thoughts)Level 6 (challenging unhelpful thoughts): cognitive restructuring (learning to challenge or swap negative thoughts for helpful ones), interpersonal skills continued (negotiation skills)Level 7 (bringing it all together): recap of all skills, mindfulness (tolerating distress), relapse prevention

The Japanese version of SPARX was developed by the Japanese companies HIKARI Lab, Inc, and SmileBoom Co, Ltd, with approval of the developers of the original version. The original English language was translated into Japanese by the fourth author (AS) who has a master’s degree in clinical psychology and is a native Japanese speaker and a fluent speaker of English. A key difference between the original and Japanese versions was the change of the Guide character’s gender from male to female. In the original version, the Guide was male, stylized to look like a Maori (the indigenous people of New Zealand) chief to give a powerful impression. However, the developers in the Japanese version were concerned that this might not suit Japanese audiences and instead adopted a female character wearing a white national costume, with a more gentle and maternal expression (Figure 2). Other modifications include the following: for all SPARX characters, the face and eyes were slightly rounded and the color schemes were made brighter to be more reminiscent of the Japanese anime esthetic; login and menu screens were slightly changed to facilitate use; by using a notification function, the user can obtain information related to mental health once a week; how to process SPARX is displayed; and as the user plays the game and proceeds through the stages, the sky color becomes brighter. There were also some necessary content changes to make the program more applicable to Japanese adult and university students as users (eg, original version: assignment/homework anxiety; Japanese version: work presentation anxiety). With the exception of these minor and complementary fixes in developing the Japanese version of SPARX, no major changes to the original were made, such as a change of the main story of SPARX. The original version was delivered on a user’s personal computer, whereas the Japanese version is delivered on a mobile phone or tablet device.

**Figure 2 figure2:**
[figure not shown]
Guide characters in the SPARX original (left) and Japanese (right) versions.

### Wait-List Control

Participants randomized to the control group will be placed on a wait list for 11 weeks; that is, until after the 1-month follow-up assessment of the group assigned to the intervention. The participants on the wait list will then be offered the opportunity to take part in the SPARX program in the same way as those in the intervention group.

### Measures

The primary outcome (Japanese version of PHQ-9) will be measured at baseline (T1), weekly throughout the interventions (T2-T7), at postassessment 1 week after the 7 intervention weeks (T8), and at 1-month follow-up (T9). Other assessments will be conducted at preassessment (T1), postassessment (T8), and 1-month follow-up (T9). Table 1 shows the schedule of assessments at various time points. At baseline (T1), demographics data will be collected, including gender, age, major in university, year of study, residence status; presence or absence of visits to psychiatric and counseling services; and presence or absence of the use of a gamified psychological program.

**Table 1 table1:** Overview of measurements.

Outcome	Scale	T1^a^	T2-T7^b^	T8^c^	T9^d^
Demographics	Developed by the authors	✓			
Depressive symptoms	PHQ-9^e^	✓	✓	✓	✓
Satisfaction with life	SWLS^f^	✓		✓	✓
Negative and positive moods	POMS-2^g^	✓		✓	✓
Social functions	EQ-5D^h^	✓		✓	✓
Rumination	RSS^i^	✓		✓	✓
Coping	Brief COPE^j^	✓		✓	✓
Stressor	DLSS^k^	✓		✓	✓
Satisfaction and acceptability	Developed by the authors				✓

^a^T1: baseline assessment (preassessment).

^b^T2-T7: assessment at each level.

^c^T8: assessment 1 week after the program.

^d^T9: assessment at 1-month follow-up.

^e^PHQ-9: Japanese version of Patient Health Questionnaire-9.

^f^SWLS: Satisfaction With Life Scale.

^g^POMS-2: Profile of Mood Scale, second edition.

^h^EQ-5D: Japanese EuroQol instrument.

^i^RSS: Japanese version of the Ruminative Responses Scale.

^j^Brief COPE: Brief Coping Orientation to Problem Experienced inventory.

^k^DLSS: Daily Life Stress Scale for undergraduates.

#### Primary Outcome Measure

The primary outcome measure is the Japanese version of PHQ-9. The PHQ-9 is a self-reported questionnaire for assessing depressive symptoms of the preceding 2 weeks [39]. The questionnaire consists of nine items evaluated using a 4-point Likert scale to indicate the extent to which the participant agrees with the values expressed in each item (0, not at all; 3, nearly every day). Higher scores indicate more severe depressive symptoms. In an earlier study [39], this scale demonstrated good internal consistency (alpha=.93) and good convergent validity (correlation coefficient with the Kessler Psychological Distress Scale: *r*=.81) in a Japanese clinical population.

#### Secondary Outcome Measures

The following sections will discuss the secondary measures used.

##### Japanese Version of the Profile of Mood States Second Edition (POMS-2)

This is a self-reported questionnaire for assessing positive and negative moods during the preceding week [40]. The questionnaire consists of 35 items evaluated on a 5-point Likert scale (0-4). For this study, we will use total mood disturbance; higher scores indicate more negative mood states. The reliability and validity of POMS-2 for a Japanese population have been reported [40].

##### The Satisfaction With Life Scale (SWLS)

This is a self-reported questionnaire for assessing satisfaction with life [41]. The questionnaire consists of five items evaluated on a 7-point Likert-type scale (1-7). Higher scores indicate more satisfaction with life. Its reliability and validity for a Japanese population have been reported [41].

##### The Japanese EuroQol Instrument (EuroQol)

This is a self-reported questionnaire for assessing health-related quality of life [42]. The questionnaire consists of five items evaluated on a 5-point Likert-type scale (1-5). Higher scores indicate worse health-related quality of life. Its reliability and validity for a Japanese population have been reported [43].

##### The Japanese Version of the Ruminative Responses Scale (RSS)

This is a self-reported questionnaire for assessing the frequency of depressive rumination [44]. The questionnaire consists of 22 items evaluated on a 7-point Likert-type scale (1-7). Higher scores indicate more frequent depressive rumination. Its reliability and validity for a Japanese population have been reported [45].

##### The Brief Coping Orientation to Problem Experienced Inventory (Brief COPE)

This is a self-rated questionnaire for assessing coping skills [46]. The questionnaire consists of 28 items evaluated on a 4-point Likert-type scale (1-4). Higher scores represent high levels of coping skills. Its reliability and validity for a Japanese population have been reported [47].

##### The Daily Life Stress Scale for Undergraduates (DLSS)

This is a self-reported questionnaire for assessing daily life stressors for undergraduates [48]. The questionnaire consists of 23 items evaluated on a 5-point Likert-type scale (1-5). Higher scores indicate more frequent stressors. Its reliability and validity for a Japanese population have been reported [48].

The final secondary outcome will be a measure of the satisfaction and acceptability of the intervention. All participants will be asked to rate four statements related to the perceived helpfulness, satisfaction with use, and the depth of understanding of the content of SPARX on an 11-point scale (0-10). Participants will also be able to write free text comments. The following questions will be asked: “How useful was this program for you [0 (not at all), 10 (very useful)]? Specifically, which components of this program were useful for you (write free text comments)?” “How satisfied are you with this program [0 (not at all), 10 (very satisfied)]?” “Please tell me about the pros and cons of this program (write free text comments)?” “How fun was this program for you [0 (not at all), 10 (very fun)]?” These items were developed specifically for the current trial.

### Statistical Analyses

The analysis for primary outcome measures will be conducted using a linear mixed model (LMM). The LMM approach was selected because of its strength in accommodating missing data and its ability to incorporate random effects into analyses. In these analyses, the dependent variable is the PHQ-9 score, and the independent variables are assignment (treatment condition, wait-list condition) and time [preassessment (T1), each session assessment (T2-T7), post-assessment (T8), and follow-up assessment (T9)], with interaction of the assignment and time as fixed-effect variables and participants as a random-effects variable. Secondary outcomes (outcome measures, process measures, and evaluation of the program) will be analyzed in the same way as the primary outcome. Subgroup analyses are not planned. For all analyses, *P*<.05 will be inferred as statistically significant. Up-to-date versions of R software (R Foundation for Statistical Computing, Vienna, Austria) will be used to analyze the quantitative data.

In the satisfaction/acceptability measure, free comments will be analyzed using thematic analysis.

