In Japan, 126 of the 135 universities (93%) have some established support systems to address the mental health needs of university students [8]. However, reaching out to professional mental health services among students is relatively uncommon [9,10] owing to several factors, including skepticism about treatment effectiveness, lack of awareness of help options, and lack of perceived need [11,12]. Therefore, access to university mental health services should be adjusted so that it is both easier and more acceptable [13]. Outside Japan, there have been many trials of internet-based and computer-delivered interventions in recent years, demonstrating significant improvements in depression compared to an inactive control (pooled standardized mean difference –0.43, 95% CI –0.63 to –0.22) [14]. Digital interventions offer important advantages: they are accessible from various locations, they can be a form of outreach to individuals who might not otherwise access traditional face-to-face services [15,16] and are more cost-effective than face-to-face treatment [17]. Moreover, digital interventions can facilitate learning and retention because users can return to the program at their convenience to practice the content more than once [18]. Given that games are familiar and particularly popular with young people in Japan [19,20], game-based interventions have the potential to be engaging and valuable self-help tools to support university students’ mental health [21,22].

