### Randomization

Participants (N=100) who fulfil all eligibility criteria will be randomized at a 1:1 ratio to either the SPARX intervention group or the wait-list control condition. The randomization sequence will be generated by the trial statistician and stratified by site. The final randomization lists will be computer-generated and concealed in a secure study database until the end of data collection/data lock.

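### The 80% power is for one two-group difference at one time point, but the planned model covers nine occasions with no deciding term, and the article gives two accounts of the primary outcome

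*Protocol article*

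**What the plan says.** The Sample Size section says that "target sample size of 90 was needed to detect an effect size of 0.60 with alpha=.05 and a power of 0.80 for a two-tailed test". It then allows for 10% dropout and states: "we will aim to recruit at least 100 (50 per group) participants to test the primary hypothesis of this study". It mentions no repeated measurements, within-person correlation or interaction.

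The Statistical Analyses section describes a linear mixed model for PHQ-9. Its fixed effects are assignment and time, the latter listed as T1, T2-T7, T8 and T9, "with interaction of the assignment and time as fixed-effect variables". Participant is the random effect, and P<.05 applies to every analysis. No term, contrast or time point is named as the primary test.

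The primary outcome is described in two ways. The Methods part of the Abstract gives the reduction in PHQ-9 over the baseline, weekly, post-intervention and follow-up measurements. The opening sentence of the Results section gives the presence of depressive symptoms at 1-month follow-up, which is T9. The hypothesis under Objectives is directional: SPARX is expected to do better than the wait list.

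**The concern.** The size calculation and the analysis appear to concern different tests. A two-group difference at one time point needs only an effect size. A test over nine occasions also needs the within-person correlation and the shape of the effect over time, and the article gives neither.

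Two things are at stake. First, the stated 80% may not apply to the test that decides the trial. Second, an overall interaction asks only whether the two mean profiles are parallel. It can be significant for a temporary mid-treatment difference, or for worsening on SPARX, so it does not answer the directional hypothesis. With two accounts of the primary outcome and several candidate terms, the deciding comparison could be picked after the data are seen.

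**Working it through.** **Inputs from the Sample Size and Randomization sections.** Effect 0.60 SD, two-sided alpha 0.05, power 0.80, N = 90, 10% dropout, 1:1 allocation, so n = 45 per arm analysed. From Statistical Analyses: nine occasions. **Assumed, because the article does not give them:** within-person correlation ρ of 0.3, 0.5 or 0.7, and the shape of the effect over time.

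**Step 1: reproduce the plan's figure.** For a two-sample t-test the noncentrality is d·√(n/2) = 0.60·√22.5 = 2.846 on 88 df. Power is 0.804 at 45 per arm and 0.795 at 44 per arm, so 90 is the smallest total that reaches 80%. Dropout: 90/0.90 = 100. Both published figures are correct for a single two-group difference.

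**Step 2: power of the overall interaction.** With time as a nine-level factor the interaction has (2−1)(9−1) = 8 df. Under the random-intercept model the noncentrality is λ = (n/2)·Σ(d_t − d̄)²/(1−ρ), referred to F with 8 and 88×8 = 704 df. Here d_t is the group difference at occasion t in SD units and d̄ is its mean over the nine occasions.

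| Effect shape | Σ(d_t − d̄)² | λ at ρ = 0.3 / 0.5 / 0.7 | Probability of P<.05 |
|---|---|---|---|
| Linear rise from 0 at T1 to 0.60 at T8, held at T9 | 0.3886 | 12.49 / 17.49 / 29.14 | 0.70 / 0.86 / 0.99 |
| 0.60 at every occasion from T2, or at T9 only | 0.32 | 10.29 / 14.40 / 24.00 | 0.60 / 0.77 / 0.96 |
| 0.60 at T3-T5 only, zero at T8 and T9 | 0.72 | 23.14 / 32.40 / 54.00 | 0.95 / 0.99 / 1.00 |
| 0.2, 0.4, 0.6, 0.6, 0.4, 0.2 at T2-T7, zero at T8 and T9 | 0.48 | 15.43 / 21.60 / 36.00 | 0.81 / 0.93 / 1.00 |

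In the last two rows a contrast at T8 or T9 would be significant only 5% of the time. Reversing the sign of the first row (a linear worsening) leaves λ unchanged, so the probabilities are the same.

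**Step 3: sensitivity to serial correlation.** Add serial correlation to the random intercept, for example V = 0.4 + 0.6·0.6^|s−t|. Then λ = δ′[(2/n)CVC′]⁻¹δ, where C forms the differences of T2-T9 from T1 and δ = Cd.
- Linear rise: λ = 8.01, power 0.44 with 81 denominator df and 0.47 with 704, so about 45%.
- Gradual mid-treatment effect (last row of the table): λ = 14.44, rejection 0.73 and 0.78, so about 76%.

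These give the lower ends of the ranges. They are not floors: pure first-order serial correlation with no participant effect, which is not the plan's model, gives 0.26 to 0.43 for the linear rise.

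**Step 4: a single contrast.** With baseline adjustment the residual SD shrinks by √(1−ρ²), where ρ is now the correlation between baseline and the chosen time point. The effective difference is 0.60/√(1−ρ²), giving power of about 0.84 / 0.90 / 0.98 at ρ = 0.3 / 0.5 / 0.7. A plain change-from-T1 contrast under the random-intercept model gives 0.67 / 0.81 / 0.96, so the kind of contrast matters as well as its time point.

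**The case against.** The strongest reply is that the article never calls the interaction the primary test and never mentions 8 df. It lists the interaction among the fixed effects. If time were continuous, the interaction would have 1 df. The Results section points to 1-month follow-up, and a comparison there is the kind of single two-group difference that the Sample Size section powers. Powering a longitudinal trial on a standardised group difference is common, and the arithmetic is right. The choice of model contrast is often left to the SAP, which is not shown.

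Much of this stands. A reader might infer that the plan has adopted the omnibus interaction as its decision rule; the text does not say so. The bracketed list of occasions makes a nine-level factor the natural reading, but only that. A reader might also infer that the trial is underpowered; Step 2 does not support this, since a linear rise gives 0.86 at ρ = 0.5 and 0.99 at ρ = 0.7. An effect of exactly zero at T8 and T9 is a constructed case that shows what the test can do, not a forecast. Whether 0.60 is too hopeful beside the pooled 0.43 in the Background is a separate question. Sample Size reports smaller estimates and explains its choice.

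What the reply does not remove is the conflict within the article. The Abstract and the Results section define the primary outcome differently, and Statistical Analyses selects neither. That is disagreement between published statements, not detail held back for an SAP.

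**Conclusion.** The point holds conditionally. It is certain that the 80% belongs to one two-group difference at one time point, that the analysis section names no deciding term or time point, and that the two accounts of the primary outcome differ. If the test is the interaction over nine levels of time, the 80% does not describe it. Power with 90 analysed then runs from about 45% to 99% for effects reaching 0.60 SD, and a mid-treatment effect that has gone by T8 and T9 is declared significant about 76% to 100% of the time. These ranges rest on assumed correlations (random intercept with ρ from 0.3 to 0.7, or random intercept plus serial correlation), assumed effect shapes and complete data on 45 per arm. The supported claim is that the stated power is not tied to an identified test, not that power is below 80%.

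**What to change.** 1. Reconcile the Abstract, Statistical Analyses and the opening of the Results section on one primary outcome and time point. The Results section points to T9, 1-month follow-up. State there that the outcome is the PHQ-9 score, if that is what is meant by presence of symptoms.
2. In Statistical Analyses, state that time is a nine-level factor and that the primary hypothesis is tested by one two-sided 5% contrast from the mixed model: SPARX minus wait list in PHQ-9 at that time point, adjusted for baseline. Label the weekly differences and the overall interaction as supportive.
3. In Sample Size, say that 90 gives 80% power for an unadjusted comparison at a single time point with an effect of 0.60, and that this is conservative for the baseline-adjusted contrast. Do not attach the 80% to a plain change score, for which it is not conservative when the correlation is below 0.5.

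The cost is a few sentences, with no extra participants or data. The sponsor gives up the option of claiming success from a mid-treatment difference alone. The change should be dated and made before the outcome data are examined by group.

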## Methods

### Study Design

This is a multicenter trial and follows a stratified randomized, parallel-group superiority design. Participants will be randomized 1:1 to an intervention arm, which will consist of the game-based computerized CBT program SPARX or a wait-list control condition. Postintervention assessments will be carried out 7 weeks after baseline assessment. The participant flow through the trial is shown in Figure 1.

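### With a single participant random effect, the PHQ-9 model assumes equal correlation across nine visits; if correlation falls with lag, the interaction and change-from-baseline tests exceed 5% type I error

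*Protocol article*

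**What the plan says.** The Statistical Analyses section of the protocol article gives the primary model. PHQ-9 is the dependent variable and assignment is one factor. The other factor is listed as "time [preassessment (T1), each session assessment (T2-T7), post-assessment (T8), and follow-up assessment (T9"). On how these enter the model, and on the random part, the section reads: "with interaction of the assignment and time as fixed-effect variables and participants as a random-effects variable". It sets P<.05 for every analysis and applies the same model to the secondary outcomes.

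The Measures section sets the schedule up to the end of treatment: "The primary outcome (Japanese version of PHQ-9) will be measured at baseline (T1), weekly throughout the interventions (T2-T7"). For the two later visits, its timing is: "at postassessment 1 week after the 7 intervention weeks (T8), and at 1-month follow-up (T9"). The Study Design section places the post-treatment visit slightly earlier: "Postintervention assessments will be carried out 7 weeks after baseline assessment". On the instrument, the Primary Outcome Measure section says: "The PHQ-9 is a self-reported questionnaire for assessing depressive symptoms of the preceding 2 weeks".

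No within-person correlation and no PHQ-9 standard deviation is given. The contrast that decides the trial is not named either. The Abstract and the Sample Size section speak of a reduction in symptoms, the model contains the interaction, and the Results section places the primary outcome at the 1-month follow-up.

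**The concern.** One participant effect with independent residuals means a random intercept, and hence compound symmetry: every pair of the nine visits has the same correlation. The schedule makes that doubtful. Neighbouring weekly scores share a recalled week, T1 and T9 are about 11 to 12 weeks apart, and depressive symptoms may drift over such a period.

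When correlation falls with lag, the model uses the average correlation over all pairs to judge the change from T1 to T8 or T9. Most pairs are close together, so that average exceeds the true long-lag correlation. The variance of the late change is then understated. At stake is the false-positive rate of the interaction test and of the reduction from baseline, on which a claim of superiority could rest.

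**Working it through.** **1. The plan's own figure.** The Sample Size section states: "A power analysis showed that a target sample size of 90 was needed to detect an effect size of 0.60 with alpha=.05", with power 0.80, two-sided, and 10% dropout.
- Normal approximation: n per arm = 2(1.960 + 0.842)² / 0.60² = 43.6, so 44 per arm (88 in total).
- Noncentral t: 44 per arm gives power 0.795 and 45 per arm gives 0.804, so 90 in total.
- Dropout: 90 / (1 − 0.10) = 100.

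The stated 90 and 100 reproduce. The checks below use 45 per arm.

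**2. Formula.** Take complete data, constant variance σ² and n per arm. The true variance of the between-arm difference in change from T1 to visit j is (2/n)·2σ²(1 − ρ₁ⱼ). A random-intercept model estimates it as (2/n)·2σ²(1 − ρ̄), where ρ̄ is the mean over the 9 × 8 / 2 = 36 visit pairs. Therefore

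SE ratio = √[(1 − ρ̄) / (1 − ρ₁ⱼ)], and type I error ≈ 2[1 − Φ(1.96 × SE ratio)].

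**3. One case by hand (assumed correlation).** AR(1) with weekly correlation 0.9, visits at weeks 0–6, 8 and 12:
- ρ̄ = 0.658; T1–T8: 0.9⁸ = 0.430; T1–T9: 0.9¹² = 0.282.
- T8: √(0.342 / 0.570) = 0.77, type I error about 12.9%.
- T9: √(0.342 / 0.718) = 0.69, type I error about 17.6%.

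**4. Simulation under no effect.** 10,000 trials per pattern, nominal two-sided 5%, weeks 0–6, 8 and 12. All correlations are assumptions. RI is the share of variance due to a random intercept.

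| Assumed pattern | SE ratio, change at T8 / T9 | Type I, T8 | Type I, T9 | Joint interaction |
|---|---|---|---|---|
| Constant 0.6 | 1.00 / 1.00 | 5.0% | 5.1% | 4.6% |
| RI 0.4 + AR(1) 0.5 | 0.92 / 0.92 | 6.9% | 7.5% | 6.6% |
| RI 0.4 + AR(1) 0.7 | 0.85 / 0.83 | 9.6% | 9.9% | 8.2% |
| RI 0.4 + AR(1) 0.8 | 0.81 / 0.77 | 10.6% | 13.1% | 8.9% |
| AR(1) 0.9 | 0.77 / 0.69 | 12.9% | 17.8% | 10.0% |
| AR(1) 0.95 | 0.76 / 0.65 | 13.9% | 20.3% | 11.1% |
| Recall overlap only (adjacent weeks 0.8, all others 0.6) | 0.96 / 0.96 | 6.4% | 6.3% | 7.2% |

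Moving T8 and T9 to weeks 7 and 11 changes little: AR(1) 0.95 then gives 13.1%, 20.4% and 11.2%.

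The recall-only row can be checked by hand. Six of the 36 pairs are one week apart, so ρ̄ = 0.6 + 0.2 × 6/36 = 0.633 and the SE ratio is √(0.367 / 0.400) = 0.96.

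**5. Is the covariance assumption the cause?** Testing the T1-to-T8 change with its own variance gives 4.4–5.2% in every pattern. So it is.

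**6. Difference in means at T8 or T9 from the same model.** With constant variance the SE ratio is 1.00 and type I error is 4.4–5.6%. If the standard deviation grows from 1 to 1.4 (assumed), the ratios are 0.89 and 0.86 and type I error is 7.5–9.7%.

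**7. Secondary outcomes (T1, T8, T9 only).** AR(1) 0.9 at weeks 0, 7 and 11 gives correlations 0.48 (T1–T8), 0.66 (T8–T9) and 0.31 (T1–T9), mean 0.48. The change SE ratio is √(0.52 / 0.52) = 1.00 at T8 and √(0.517 / 0.686) = 0.87 at T9.

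**The case against.** The strongest reply is that the article never says random intercept only, and that a residual covariance structure is the kind of detail an article leaves to the analysis plan. That is fair as a caution: the unseen plan may add one. But the article does state the term that generates the within-person correlation, and it states only that one. An analyst following this text would fit compound symmetry, so the criticism is of a stated model and not of silence.

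Three stronger readings are tempting, and the document does not support them.

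- **All standard errors at T8 and T9 are too small.** They are not: step 6 shows that the arm difference in means is sound under constant variance. The Results section can be read as pointing to that contrast at T9. However, the Abstract and the Sample Size section speak of reduction, and the model includes the interaction; those are the affected tests.
- **The 2-week recall proves that correlation must fall with distance.** It shows only that neighbouring weekly visits overlap. T1 shares no recalled week with T4 any more than with T9. Overlap alone gives about 6–7%; the larger figures need longer-range decay, which is plausible but not quantified in the article.
- **Secondary outcomes suffer equally.** With three visits, the T8 change is essentially unaffected in the case checked in step 7.

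**Conclusion.** The point holds in conditional form. The stated model implies equal correlation across nine visits, which is unlikely for this schedule. If correlation decays with lag, the assignment-by-time test and the change-from-T1 contrasts are anticonservative: about 7–14% at T8, 7–21% at T9 and 6–11% for the joint interaction. Every decaying pattern tried exceeded 5%, and constant correlation gave about 5%.

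These figures rest on assumed correlations, 45 per arm, complete data and a random intercept with independent residuals. They show a risk with a range. A reader might infer that the 5% level is known to fail in this trial; the article has no correlation data to establish that. The sample size is not in question.

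**What to change.** For PHQ-9, replace the single participant random effect with a repeated-measures model that keeps the same fixed effects and has an unstructured covariance over the nine visits, fitted by REML with Kenward-Roger degrees of freedom. Pre-specify the fallback if it does not converge: participant random intercept plus continuous-time AR(1) in weeks, which also accommodates the longer gap before T9. The fallback needs one set of visit weeks, so the T8 timing in Study Design and in Measures must be reconciled. The same text should name the contrast that decides the trial, because exposure to the problem depends on it.

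The cost is a sentence or two before analysis, with no new data or participants. The downsides are 9 × 10 / 2 = 45 covariance parameters from about 90 participants, which is why the fallback is needed, and somewhat wider intervals. For the three-visit secondary outcomes the same change is harmless and matters mainly for the T9 change.
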